### Breath testing

A study published in 2004 [37] demonstrated that 100% of participants with fibromyalgia had small intestinal bacterial overgrowth (SIBO) as determined by an oral lactulose challenge. To the best of our knowledge, this finding has not been replicated.

Fermentation of ingested carbohydrates by intestinal bacteria can result in gas production and may be associated with gastrointestinal distress [38]. We aim to conduct three separate hydrogen-methane breath tests on each participant. Initially, an oral glucose challenge, followed by fructose and lactulose challenges.

#### Breath test preparation

Prior to breath testing, four weeks must elapse after gastroenteritis, antibiotic therapy, or undergoing colonoscopy. Before commencing each test, participants will be asked to avoid probiotics and probiotic-containing foods for at least three days, follow a restricted low fermentable diet [39] for at least one full day, and fast overnight (12 hours minimum). On the day of each test participants will be asked to clean their teeth on awaking and avoid vigorous exercise. No food is permitted until sample collection is complete.

#### Conducting breath tests

All glucose breath tests will be conducted at the study site. These, and any subsequent breath tests conducted at the study site, will begin by collecting 3 baseline breath samples, at 1-minute intervals. To optimise gas exchange, each sample will be collected after a 15-second breath hold [40]. Participants expire into a GaSampler test kit (QuinTron, Milwaukee, WI [QT] 00892,) and 30cc of breath will be extracted from the sample holding bag with a leur-lock syringe (QT02741) with 1-way stopcock (QT01727-V). These end-alveolar samples are then injected into the BreathTracker SC (QuinTron) through a drying tube (QT01135-K) containing BreathPrep™ desiccant (QT01161-C), and a dust trap (QT01140-K).

At-home breath sample collection utilises the EasySampler test kit (QT04214) with detailed instructions and 13 sterile glass vials (QT02602). A single baseline sample precedes substrate ingestion.

For each breath test, whether at the study site or using an at-home kit, a single breath sample will be collected at 15-minute intervals after substrate ingestion, each after a 15-second breath hold. No fluid is permitted in the first 60 minutes after substrate ingestion; thereafter plain water may be taken during the first 10 minutes after collection of each breath sample. Food is not permitted until sample collection is complete.

Home-collected breath samples are to be returned to the study site within 5 days. This allows ample time for shipping delays, ensuring samples are received and analysed within the manufacturer’s specified 14-day viability period. Breath samples are extracted from the test tubes using the AlveoVac extraction system (QT02637), with vial adapter (QT02688) and dust trap (QT01140-K) fitted. Results are manually transcribed then entered into a Microsoft® Excel® spreadsheet.

The BreathTracker, maintained and calibrated in accordance with the manufacturer’s guideline [41], has a resolution of 1ppm for hydrogen (H_2_) and methane (CH_4_), and 2% for carbon dioxide (CO_2_). Accuracy is ± 3ppm or ± 5% of full scale for H_2_ and CH_4_, and ± 1% for CO_2_, linear range 0-150ppm for H_2_, 0-75ppm for CH_4_ and 0.1%-7% for CO_2_. The equipment automatically corrects samples for contamination with room or dead-space air by detecting the CO_2_ concentration, thus giving the true alveolar concentration of H_2_ and CH_4_ [41]. Where CO_2_ recoveries are insufficient, the sample is declared invalid. Data are reported in ppm, manually recorded, then entered into a Microsoft® Excel® spreadsheet for later analysis.

#### Symptoms during breath testing

For each breath test, a checklist will be completed to confirm participants’ adherence to pre-test instructions. Symptoms present at baseline are graded on a 0-10 scale, where 0 is “not present” and 10 is “the most severe”. The symptom record will be updated every 15 minutes, after collection of each breath sample.

#### Glucose breath test & oral glucose tolerance test

Glucose is a well-absorbed monosaccharide, used to detect bacterial overgrowth in the proximal small intestine [38]. An oral dose of 75g is used to confirm a diagnosis of diabetes mellitus (DM), and 50g is commonly administered during pregnancy to predict gestational DM [42].

For this test, 50g of anhydrous d-glucose (FCC-25304, ECP Labchem Ltd, NZ), dissolved with 250mL of water, is given after baseline data is collected, as per the most current guideline [38]. Breath samples are collected for 2.5 hours.

To monitor the glycaemic response, capillary samples will be obtained from a finger-prick at baseline, then 60, and 120 minutes after glucose ingestion with a single-use 23G disposable lancet (Unistik® 3, Owen Mumford, UK) and blood glucose monitor (CareSens® N, i-SENS, Inc., Seoul, Korea), range 1.1 - 33.3 mmol/L.

#### Fructose breath test

Fructose is a monosaccharide that is less readily absorbable than glucose. Early fermentation may indicate bacterial overgrowth in the proximal gut [43] and delayed fermentation suggests malabsorption, which may be associated with gastrointestinal distress [38]. For this test, 25g fructose (FCC-24704, ECP Labchem Ltd, NZ), dissolved in 250g of water, will be administered after capturing baseline data as above. Samples are collected for 3 hours.

#### Lactulose breath test

Lactulose is a synthetic disaccharide, for which humans lack an enzyme capable of digesting. Therefore, it passes into the colon unchanged, where it may act as an osmotic laxative and may also be fermented by colonic microbes. At doses that do not cause osmotic diarrhoea, lactulose has been used as a probe to evaluate oro-caecal transit time by onset of hydrogen production, with early rises in breath gases being considered predictive of SIBO [38]. The test substrate was 15mL of lactulose BP 3.34g/5mL (Laevolac, Douglas Pharmaceuticals, NZ) in 250mL of water. Sample collection is over 3 hours.

#### Survey data

Due to the complexity of fibromyalgia, and the multi-system symptoms that might affect a person with the condition, a comprehensive questionnaire has been developed on REDCap, which integrates the following validated tools:ACR fibromyalgia diagnostic criteria, 2016 [2]Revised Fibromyalgia Impact Questionnaire [44, 45]Rome IV [8, 46] – the current diagnostic criteria for FGIDs from the Rome FoundationFunctional Bowel Disorder Severity Index [47, 48]Headache Symptom Questionnaire [49, 50]General Anxiety Disorder-2 [51]Medical Outcomes Study Sleep Scale [52]Short Form Survey -36 [53, 54] – for measures of health-related quality of lifeOral Health Questionnaire [55]

Additional questions are included to capture other medical diagnoses, and symptoms related to environmental mould exposure. To assess current dietary intake, DietID®, a diet quality photo navigation tool will be used [56].

### Statistical analysis

All data will be anonymised and saved in password protected computer hosted on the University of Sydney’s Data Management System. Statistical analysis will be performed using specialist software. The level of significance will be set at *p* < 0.05.

Descriptive statistics will be used to detail the characteristics of the cohort, and the students’ t-test will be employed to compare participants and controls. Anthropometrics, symptom prevalence, scores and co-morbidities will be compared using univariate and multivariate analysis of variance, as appropriate.

After clustering data according to conventions appropriate to each of the questionnaires in the participant survey, group differences will be assessed using students’ t-tests, Wilcoxon signed-rank test chi-squared tests, and logistic regression, as appropriate.

For microbiome analyses, after stratification by age-groups to allow for variances that may be associated with reproductive life-stages, correction for multiple comparisons (e.g., using Benjamini–Hochberg FDR) and normalised operational taxonomy units will be evaluated using Pearson's correlations. Strength of associations with clinical variables will be tested using Spearman's Rho. Further statistical analysis of the data will be performed using machine learning methods.

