### Participants and recruitment

This is a prospective, single-centre, cross-sectional case-controlled, observational study. We aim to recruit at least 100 adult women meeting fibromyalgia diagnostic criteria and a minimum of 50 matched controls. Limiting the study to females reduces the confounding influence of gender difference on gastrointestinal function and the gut microbiome. To determine suitability for inclusion as a participant or as a healthy control, initial screening will be conducted via a survey hosted on Research Electronic Data Capture (REDCap) (via the University of Sydney). Prospective volunteers will then be contacted directly by the study co-ordinator to confirm suitability and book appointments as appropriate.

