#### Inclusion and exclusion criteria

Women aged 18 to 75 years, meeting fibromyalgia criteria as defined by the American College of Rheumatology (2016) (ACR2016), or with a formal diagnosis by a medical practitioner, and willing to comply with study requirements, including travelling to the study site in Auckland, NZ, will be invited to join the study.

Exclusion criteria for both groups include being a current smoker, having a diagnosis of diabetes mellitus, being pregnant or breastfeeding, having any major comorbid illness (e.g., malignancy, active inflammatory or metabolic disease), or being unable to withhold anti-inflammatory medication for at least 48 hours. At least 4 weeks must lapse after any antibiotic treatment before enrolment.

Healthy controls must meet the same criteria, except they must *not* meet criteria for fibromyalgia.

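### Student's t-test is named for case-control comparisons while recruitment minima stand at 100 and 50; Welch's test would keep standard errors right if the groups differ in spread

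*Protocol article*

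**What the plan says.** The Statistical analysis section of the protocol article, after the descriptive statistics, states without qualification that Student's "t-test will be employed to compare participants and controls". It adds: "Anthropometrics, symptom prevalence, scores and co-morbidities will be compared using univariate and multivariate analysis of variance, as appropriate". For questionnaire data, "group differences will be assessed using" a list that reads "t-tests, Wilcoxon signed-rank test chi-squared tests, and logistic regression, as appropriate". "The level of significance will be set at" p < 0.05. No unequal-variance version is named, and pooling is not mentioned either.

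On group sizes, Participants and recruitment states: "We aim to recruit at least 100 adult women meeting fibromyalgia diagnostic criteria and a minimum of 50 matched controls". The Sample size section asks for no fewer than 55 in each group. On eligibility, "Healthy controls must meet the same criteria, except they must" not satisfy the criteria for fibromyalgia. No SD is given for any outcome.

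**The concern.** Student's t-test, as the name is normally used, estimates one common variance from both groups. With equal group sizes this does no harm, because the pooled standard error equals the correct one whatever the two SDs are. With unequal sizes, the larger group dominates the pooled variance. If the larger group is the more variable one, the standard error is too big: intervals are too wide and real differences are missed. If the smaller group is the more variable one, the standard error is too small and false positives rise. Classical ANOVA pools in the same way, so sending a score through ANOVA does not avoid the issue.

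Here the larger group is the cases. Controls are selected not to have fibromyalgia. On bounded symptom and impact scales, such as the fibromyalgia criteria themselves or the Revised Fibromyalgia Impact Questionnaire, they can be expected to sit nearer the floor while cases spread out. That is an inference from the eligibility rules, not a stated figure. At stake is mainly precision and power in the case-control tables.

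**Working it through.** **Inputs.** Group sizes of 100 and 50 come from Participants and recruitment. The figure of 55 controls comes from Sample size. Alpha is 0.05 from Statistical analysis, taken as two-sided because the side is not stated. SD ratios are assumptions. The protocol gives no SD, standard error or power for any t-test, so it has no figure of its own to reproduce on this point.

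**Formula.** With case size and SD n1, s1 and control size and SD n2, s2, the ratio of pooled to true standard error is

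R = sqrt{ [((n1−1)s1² + (n2−1)s2²)/(n1+n2−2)] × (1/n1+1/n2) ÷ (s1²/n1 + s2²/n2) }.

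**100 v 50, by hand** (1/100 + 1/50 = 0.03; n1+n2−2 = 148):
- SD 2:1. Pooled variance (99×4 + 49×1)/148 = 3.007; ×0.03 = 0.0902. True 4/100 + 1/50 = 0.0600. R = sqrt(1.503) = 1.226.
- SD 1.5:1. (99×2.25 + 49)/148 = 1.836; ×0.03 = 0.0551. True 0.0425. R = 1.138.
- SD 1:1.5. (99 + 49×2.25)/148 = 1.414; ×0.03 = 0.0424. True 0.0550. R = 0.878.
- SD 1:2. (99 + 49×4)/148 = 1.993; ×0.03 = 0.0598. True 0.0900. R = 0.815.

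**Type I error and power.** In the normal approximation, actual type I error is 2×[1 − Φ(1.96R)]. If the true difference gives Welch's test 80% power, it is 1.96 + 0.842 = 2.802 true standard errors, and Student's power is about Φ(2.802 − 1.96R). At R = 1.226 this is Φ(0.399) = 65.5%; at R = 1.138 it is Φ(0.571) = 71.6%. Simulation of normal data (40,000 to 100,000 data sets per setting for the rows at 1.5 and 2) agrees.

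| Case:control SD (assumed) | R | Type I, formula | Type I, simulated | Power where Welch has 80% |
|---|---|---|---|---|
| 2:1 | 1.226 | 1.6% | 1.6–1.8% | 65% |
| 1.5:1 | 1.138 | 2.6% | 2.6% | 71% |
| 1.25:1 | 1.077 | 3.5% | 3.4% | about 76% (formula) |
| 1:1 | 1.000 | 5.0% | 5.0% | 80% |
| 1:1.25 | 0.929 | 6.9% | 6.8% | – |
| 1:1.5 | 0.878 | 8.5% | 8.4–8.6% | – |
| 1:2 | 0.815 | 11.0% | 11.1–11.2% | – |

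Welch's test stays at about 5% throughout (4.8% to 5.3% across the simulation runs). With equal variances, Student's and Welch's power were 79.6% v 79.5% in one run and 80.2% v 79.9% in another.

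**100 v 55.** SD 2:1 gives (99×4 + 54)/153 = 2.941; ×0.02818 = 0.0829; true 0.0582; R = 1.194. Power is Φ(2.802 − 2.340) = 68%. At 1.5:1, R = 1.119. In the other direction, simulated type I error is about 8% at 1:1.5 and about 10% at 1:2.

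**55 v 55.** With n1 = n2 = n the pooled variance is (s1²+s2²)/2, and multiplying by 2/n gives (s1²+s2²)/n, which is the true variance. R is exactly 1 for every SD ratio.

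**The case against.** The strongest reply is that the article never says variances are pooled. Student's t-test is often a loose label in journal text, and an analysis plan that is not shown could specify the unequal-variance form. This has some force, but the article does not leave the test open. It names one, and that name conventionally means the pooled form. Naming Welch's test removes the doubt either way.

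Four further points limit the claim, and they stand.
- **Scope.** A reader might infer that every continuous score and marker is tied to this test. The text does not say so. The second mention is one option in a list to be used as appropriate, scores may go to ANOVA, blood, urine and breath markers are not individually assigned a test, and microbiome data go to correlations and machine learning. The rank option in the list is the signed-rank test, a procedure for paired data, so it is not a ready alternative for two independent groups.
- **Allocation.** A reader might take 2:1 as the fixed design. The figures are minima, the Sample size section asks for at least 55 controls, and attrition is expected but not quantified. The final ratio is therefore unknown. Moving to 55 controls with 100 cases helps only a little.
- **Direction.** A reader might infer inflated false positives. The only mechanism the document supports is controls bunched near the floor, which makes the larger group more variable and the test conservative. Nothing suggests that controls vary more.
- **Floor.** The floor argument is itself limited. Controls are barred from meeting fibromyalgia criteria and from major comorbid illness, but irritable bowel syndrome, headache, anxiety and poor sleep are not listed as exclusions, and several of the instruments measure these.

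It can also be said that controls are relatives, cohabitants or friends of cases, so that Welch's test, like Student's, ignores any pairing. That is true, but it is a separate question and does not make pooling any safer.

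**Conclusion.** The point holds as a modest, conditional one. The named test is miscalibrated if two things happen together: the groups end well away from equal size, and their SDs differ. Over assumed SD ratios of 1.5 to 2 with cases more variable, the cost at 100 v 50 is intervals 14% to 23% too wide and power of about 71% to 65% in place of 80%. At a ratio of 1.25 the intervals are about 8% too wide. The reverse direction, with type I error of about 8% to 11%, is arithmetically possible but has no support in the document. These figures assume normal data, independent groups and two-sided testing. At equal group sizes the problem does not arise.

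**What to change.** In the Statistical analysis section, replace Student's t-test with Welch's unequal-variance t-test wherever a t-test compares a continuous variable between cases and controls, and report the difference with its Welch 95% CI. Where such a variable goes through univariate ANOVA, use heteroscedasticity-robust standard errors (for example HC3). This does not cover the planned multivariate ANOVA, nor any pairing of cases with the controls they invite; both need their own decision.

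The cost is a short wording change and a software option. In the simulations the power loss under equal variances was at most 0.3 percentage points. No change to recruitment or data collection is needed.

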#### Sample size

Based on 2002 data, the estimated prevalence of fibromyalgia in the NZ population (~5 million) is 1.5% [23]. Up to 98% of women with fibromyalgia may have at least one FGID [24], thus for alpha of 0.05 and confidence interval (CI) of 95%, no less than 55 participants and 55 controls are required.

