#### Recruitment

A study website has been designed to enhance the recruitment phase of this study. The site contains information about the project, details on the study design, and a link to the eligibility survey, hosted on REDCap. Links to this website, along with summary information, will be provided to a range of health professionals thought to have interactions with people with fibromyalgia. Printed flyers will be distributed to medical centres, allied health clinics and pharmacies, and displayed on community and library noticeboards within a 5km radius of the study site. As each participant completes submission of study samples, a report detailing the available results will be sent to them and their medical practitioner. A brief outline of the study will be included, along with a recruitment flyer.

In addition, the study will be promoted via advertisements and social media posts via support groups and community pages, including the Facebook page of Fibromyalgia NZ.

Volunteers with fibromyalgia will be requested to invite a healthy adult female who is a family member (sister, daughter, mother), household cohabitant or close friend to participate to form our control group. Where numbers for controls are lacking, age-matched controls will be sought via social and professional networks.

In lieu of financial compensation to volunteers, each participant will receive a report detailing results from tests analysed at the study site. Together these have a retail value of more than NZ$500.

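### The only rank test named for case-control differences in the survey data is a paired test, but the planned groups are unequal and no one-to-one paired analysis is described

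*Protocol article*

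**What the plan says.** In the protocol article, the Statistical analysis section introduces the survey comparisons with "After clustering data according to conventions appropriate to each of the questionnaires in the participant survey, group differences will be assessed using". The list that follows is t-tests, then "Wilcoxon signed-rank test chi-squared tests, and logistic regression, as appropriate". No other rank test for comparing two groups appears in the section. Spearman's rho is named, but only for the strength of association between microbiome measures and clinical variables.

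Participants and recruitment describes the design: "This is a prospective, single-centre, cross-sectional case-controlled, observational study". It sets the target as "at least 100 adult women meeting fibromyalgia diagnostic criteria and a minimum of 50 matched controls". The Sample size section gives a different floor: "no less than 55 participants and 55 controls are required".

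Controls come by two routes, both described under Recruitment. The first is by invitation from a case: "Volunteers with fibromyalgia will be requested to invite a healthy adult female who is a family member", with household members and close friends also allowed. The second is a fallback: "Where numbers for controls are lacking, age-matched controls will be sought via social and professional networks". Study procedures places completion of the questionnaire at the first visit.

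**The concern.** The signed-rank test ranks the differences within pairs, so it needs exactly one control value for each case value. The comparison it is assigned to is between two groups planned at 2:1, measured once. An analyst who judges a rank test suitable for a skewed survey score finds only this one on the list. The choice is then to depart from the list or to cut the data down to pairs. Cutting down wastes cases who have undertaken a demanding set of tests. It also raises the question of which case each fallback control should be paired with, which the article does not answer.

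**Working it through.** **No planned figure to reproduce.** The article gives no power, effect size or within-pair correlation for the survey comparisons. Its one calculated figure, 55 per group, does not bear on this point and cannot be rebuilt from its stated inputs. As single-proportion precision, n = 1.96² × 0.98 × 0.02 / d² gives 31 at d = 0.05, and reaches 55 only at an unstated d = 0.037.

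**Does the test fit the design?**

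- A within-person reading is not available: the study is cross-sectional and the stated contrast is between groups.
- A one-to-one reading is not described: the target is at least 100 against a minimum of 50, and no section provides a record linking each control to a case.
- A standard signed-rank routine given 100 and 50 values stops with an error because the lengths differ.

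**How many cases can be used?** With 100 cases and 50 controls, the number of pairs is at most min(100, 50) = 50, leaving at least 100 − 50 = 50 cases (50%) unused. With 100 cases and 55 controls, 45 are unused. With 55 and 55, the counts alone leave none unused.

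**What does that do to precision?** In units of the outcome SD, with no within-pair correlation:

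- All participants: SE = √(1/100 + 1/50) = 0.173.
- 50 v 50: SE = √(1/50 + 1/50) = 0.200, which is 15% larger.
- Difference detectable with 80% power, (1.96 + 0.84) × SE: 0.485 SD against 0.560 SD.
- With t distributions in place of the normal: 0.488 SD for 100 v 50 and 0.572 SD for 50 pairs. Power at 0.5 SD is 0.818 and 0.688.

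**What if the pairs are genuinely alike?** With within-pair correlation ρ, the paired SE is √(2(1 − ρ)/50) = √(0.04(1 − ρ)). Setting this equal to √0.03 gives 1 − ρ = 0.75, so break-even is near ρ = 0.25 on this rough comparison. Simulation of the rank tests puts it near 0.3. The settings were 4,000 runs each, normal outcomes, an assumed 0.5 SD difference and two-sided alpha 0.05:

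| ρ | Rank-sum, 100 v 50 | Signed-rank, 50 genuine pairs |
|---|---|---|
| 0 | 0.80 | 0.67 |
| 0.2 | 0.82 | 0.76 |
| 0.3 | 0.82 | 0.81 |
| 0.4 | 0.82 | 0.86 |
| 0.5 | 0.84 | 0.92 |

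If pairs are arbitrary, signed-rank power stays at about 0.66 to 0.68.

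**A caution about the plain rank-sum test.** When 50 of the cases are paired with the controls and this is ignored, the rank-sum test is conservative. Its simulated type I error was 0.050 at ρ = 0, 0.037 at 0.2, 0.023 at 0.4 and 0.018 at 0.5. That argues for using the matched sets where the link is known.

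**The case against.** The strongest reply is that this is a slip of the pen. The two Wilcoxon tests are easily confused, rank-sum was probably meant, and the routine would refuse the full data rather than return a wrong answer. The list also ends by leaving the choice to suitability, and the preceding paragraph sends scores to analysis of variance as well. So it is not fixed that every skewed score goes to signed-rank. All of this stands and lowers the weight of the point. It does not remove it: the freedom to choose is among the listed tests, and no listed rank test suits two unequal groups.

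A second reply is that the controls are matched. Cases invite relatives, cohabitants and friends, so some pairs will be real, and signed-rank is legitimate for those. This stands too. But using only such pairs still leaves at least half of 100 cases out, and the fallback age-matched controls are not described as tied to a particular case.

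Three stronger readings are tempting, and the article does not support them:

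- A reader might infer that results will depend on row order because pairs must be invented. That would happen only if someone cut the groups to equal length and paired them arbitrarily. The article does not propose this, and the software error would stop an unthinking run.
- A reader might infer a certain loss of power. The loss depends on an assumed effect and on a low within-pair correlation, and it reverses when the correlation is above about 0.3.
- A reader might infer that the neighbouring t-test is unpaired, making the list openly inconsistent. The article does not say whether it is paired or unpaired.

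Finally, 100 and 50 are floors rather than final sizes. At 55 and 55, equal counts would force no discarding, although equal counts do not by themselves make pairs.

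**Conclusion.** The test as named does not fit the comparison it is assigned to, and that follows from the article's own text without any assumption. At the recruitment minimums, at least 50 of 100 cases could not enter it. The effect on power is conditional. With an assumed 0.5 SD difference and normal outcomes, the change from rank-sum on everyone to signed-rank on 50 pairs runs from a loss of about 0.13 (0.80 to 0.67) at zero correlation, through roughly nothing at 0.3, to a gain of about 0.08 (0.84 to 0.92) at 0.5. The article supplies neither the effect nor the correlation. Because rank-sum was probably intended and the misuse would be noticed when the analysis was run, this is a correction to make before analysis. It does not threaten the study.

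**What to change.** In the Statistical analysis section, replace the signed-rank test with the Wilcoxon rank-sum (Mann-Whitney) test on all cases and controls. If a paired analysis is wanted, name it separately as secondary, restrict it to genuine case-control pairs, and use signed-rank there. This costs a change of name and, if the secondary analysis is kept, one added sentence. It needs no new participants or measurements.

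A further step is optional. If the link between a case and the control she invited is recorded, a method that allows for matched sets and keeps every case can be used, such as a clustered rank-sum test or a mixed model. It would avoid the conservatism of the plain rank-sum test. This costs more than wording: it needs a matched-set identifier, which no section describes, recorded at enrolment or recovered for women already enrolled. Controls found through the fallback route would be entered as unlinked unless they are tied to a case when recruited.
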